## Abstract

**Background**: Cancer cachexia and sarcopenia are highly prevalent complications affecting up to 50% of patients with cancer and are associated with increased treatment toxicity, poorer functional outcomes, and reduced survival. Early identification of muscle deterioration during hospitalization remains challenging. **Objective**: To evaluate the change in dominant-hand handgrip strength between hospital admission and discharge in hospitalized oncology patients. **Methods**: This prospective longitudinal study will evaluate hospitalized adults with confirmed malignancy and an expected hospital stay of ≥5 days. Daily handgrip strength and sEMG assessments will be performed as exploratory secondary measures to characterize temporal patterns of muscle function during hospitalization. Baseline and discharge evaluations will additionally include bioelectrical impedance analysis, validated patient-reported outcome measures (SARC-F, EORTC QLQ-C30, PSQI), and serum biomarkers related to inflammatory and nutritional status. Linear mixed models will be used to evaluate longitudinal changes and associations between functional, electrophysiological, and biochemical parameters. **Expected results**: The study aims to characterize trajectories of muscle function decline during hospitalization, identify candidate biomarker signatures for cachexia detection, and evaluate neuromuscular fatigue patterns using sEMG. **Conclusions**: This protocol proposes a feasible multimodal framework for monitoring skeletal muscle deterioration during acute oncology hospitalization and may inform future interventional strategies targeting cancer-related cachexia and sarcopenia.

## 1. Introduction

Skeletal muscle deterioration is a critical and common complication in cancer, yet it remains frequently underdiagnosed across different tumor types and disease stages. Cancer cachexia is a multifactorial metabolic syndrome characterized by progressive loss of muscle mass and function, affecting up to 50% of cancer patients and associated with significantly reduced survival [1,2,3,4,5,6].

Its pathophysiology involves a complex interplay between proinflammatory cytokines, an imbalance between protein synthesis and degradation, and systemic metabolic dysfunction. Notably, muscle loss during hospitalization can progress rapidly, with measurable declines occurring within 5 to 10 days [7,8,9].

Current clinical assessment of cancer-related muscle loss largely relies on imaging-based estimates of muscle mass or subjective clinical evaluation. However, these approaches are often impractical for repeated inpatient monitoring, involve radiation exposure, and provide limited insight into neuromuscular function or fatigue mechanisms [2,4,10,11]. Consequently, early detection of functional muscle deterioration during acute hospitalization remains challenging.

The combination of handgrip strength (HGS), surface electromyography (sEMG), and bioimpedance may provide a non-invasive and objective method to assess neuromuscular integrity and detect fatigue patterns, among other parameters; however, some of these techniques remain underutilized in oncology populations, especially during hospitalization. Furthermore, the integration of multiple biomarkers reflecting different pathophysiological axes (inflammatory, nutritional, catabolic) has not been systematically evaluated during short-term inpatient follow-up.

This protocol aims to address these gaps by proposing a comprehensive, multimodal assessment framework specifically designed for hospitalized oncology patients. The approach integrates functional measures (HGS), body composition analysis (bioimpedance), neuromuscular characterization (sEMG), patient-reported outcomes, and serum biomarkers to provide an integrated evaluation of muscle status during hospitalization.

## 2. Objectives

### 2.1. Main Objective

The primary objective is to quantify the change in dominant-hand handgrip strength (HGS) between hospital admission and discharge in hospitalized oncology patients, using the Southampton protocol [12].

### 2.2. Secondary Objectives

Secondary objectives include the characterization of daily trajectories of muscle function, neuromuscular fatigue, body composition, and biomarker profiles during hospitalization.

To describe in-hospital trajectories of muscle function through daily assessment of neuromuscular fatigue using sEMG (MDF, MNF, fatigue slope, and, when applicable, time to failure).To determine admission-to-discharge changes in phase angle derived from bioimpedance and in serum indices related to inflammation and nutritional status (Prognostic Nutritional Index, Neutrophil-to-Lymphocyte Ratio, CRP/albumin ratio, CRP/prealbumin ratio).To evaluate associations between muscle deterioration and patient-reported outcomes related to sleep quality, quality of life and symptoms, including the SARC-F, EORTC QLQ-C30, and PSQI scales.

An additional exploratory objective is to identify candidate clinical, functional, electrophysiological, and biochemical variables associated with greater muscle deterioration during hospitalization, with the aim of informing future hypothesis-driven studies.

## 3. Materials and Methods

### 3.1. Study Design

This is a prospective, longitudinal cohort study including hospitalized cancer patients, evaluated from admission to discharge. This protocol was developed in accordance with the STROBE recommendations for observational research. In addition, selected SPIRIT items were considered to enhance transparency and completeness in the reporting of protocol procedures, outcome definitions, and data management plans, adapted to the observational nature of the study. The study will be conducted in accordance with the Declaration of Helsinki and the principles of Good Clinical Practice applicable to non-interventional clinical research. It will take place in the Oncology Ward of the Hospital Clínico Universitario de Salamanca (Salamanca, Spain) during the period March–November 2026.

Trial registration: ClinicalTrials.gov Identifier: NCT07387770, Protocol version: Version 2.0, dated 24 June 2026.

Any protocol modifications affecting study objectives, eligibility criteria, outcome measures, or analytical procedures will be documented, dated, and reported in subsequent publications arising from this project. Study findings will be disseminated through peer-reviewed scientific publications, conference presentations, and academic communications. Results will be reported regardless of the direction or magnitude of the findings.

### 3.2. Participants

#### Sample and Recruitment

The sample will consist of adults (≥18 years) with a confirmed diagnosis of malignant neoplasm admitted to the Oncology Ward of the Hospital Clínico Universitario de Salamanca, recruited consecutively during the period March–November 2026. Eligible patients must have an expected hospital stay of at least 5 days, a functional status of 0–2 according to the Eastern Cooperative Oncology Group (ECOG) scale, and the ability to provide informed consent, complete questionnaires, and perform voluntary contractions required for functional testing. These criteria were established to ensure participant safety, feasibility of assessments, and data quality in the context of repeated bedside neuromuscular evaluations.

Exclusion criteria include contraindications to strength assessment, such as recent fractures, acute musculoskeletal injuries, or pain limiting safe performance of the tests. Patients with severe neurological impairment preventing reliable functional assessment or significant cognitive deficits affecting comprehension or adherence to instructions will also be excluded. In addition, participants with implanted electronic devices will not be included, in accordance with the contraindications or precautions for bioimpedance measurements. Patients with extensive skin lesions or dermatological alterations at electrode placement sites that prevent safe and proper surface electromyography (sEMG) recordings will be excluded.

Cancer stage and current treatment (chemotherapy, immunotherapy, radiotherapy, or supportive care) will be recorded.

A consecutive sampling strategy will be used. Potential participants will be identified in coordination with the medical team, with oncologists referring eligible patients according to the inclusion and exclusion criteria. Nursing staff will also collaborate by providing relevant clinical and care information and by facilitating the scheduling of assessments at times compatible with routine patient care.

A screening log will be maintained throughout the recruitment period to document the number of patients assessed for eligibility, reasons for exclusion, refusal to participate, and recruitment outcomes. When available, basic demographic and clinical information of excluded patients will be summarized in aggregate form to assess the representativeness of the recruited cohort.

The sample size was estimated based on the expected change in HGS, defined as the difference between admission and discharge in the dominant hand, which constitutes the primary outcome. A clinically meaningful difference of 4–5 kg was assumed, based on previous studies in oncology populations, with a standard deviation of 4–5 kg for change in HGS, consistent with prior literature in cancer and comparable adult populations [13].

Using a two-sided significance level of 0.05 and a statistical power of 80%, the estimated minimum sample size ranged between 16 and 25 participants. However, given the exploratory and hypothesis-generating nature of the study, a larger sample size was selected to improve precision and robustness of estimates. A target sample of 50 participants was therefore established. Assuming a potential dropout rate of approximately 10%, the study aims to recruit 55 participants in total. The recruitment period was established based on the expected volume of oncology admissions at the participating institution and previous clinical experience with similar patient populations. Considering the anticipated number of eligible admissions and the target sample size of 55 participants, the planned recruitment window from March to November 2026 is considered feasible. Recruitment feasibility is supported by the high volume of oncology admissions managed by the Medical Oncology Department of the Complejo Asistencial Universitario de Salamanca, a tertiary referral center serving multiple health areas. Although precise screening figures are not available, previous institutional activity suggests that recruitment of 55 participants within the planned recruitment period is achievable.

This approach is consistent with phase II signal-seeking or feasibility study designs, aiming to obtain more stable estimates of HGS changes and variability, reduce the impact of missing data, and enable exploratory multivariable analyses of limited complexity, in line with methodological recommendations for pilot and feasibility studies [14,15,16,17,18]. Daily repeated measurements will not be included in the sample size calculation and will be analyzed as exploratory longitudinal outcomes.

The sample size calculation was based exclusively on the primary outcome and was not intended to support adequately powered predictive multivariable modeling. Accordingly, longitudinal mixed-effects models and multivariable analyses will be considered exploratory and hypothesis-generating, primarily aimed at estimating effect sizes and assessing feasibility. To reduce the risk of overfitting, the number of covariates will be limited a priori to a small set of clinically relevant variables selected based on prior evidence and clinical relevance. Results from these analyses will therefore be interpreted with appropriate caution.

### 3.3. Outcome Measures

#### 3.3.1. Main Outcome Measure

HGS will be measured in both hands at each visit using the standardized Southampton protocol [12], performing three attempts per hand and recording the maximum value for each hand [19]. This bilateral measurement reduces the risk of underestimating true maximal strength, as a substantial proportion of individuals may achieve their highest value in the non-dominant hand [20]. To avoid multiplicity of endpoints and ensure consistency with regulatory recommendations, including those of the U.S. Food and Drug Administration (FDA) [21], the primary outcome is prespecified as the absolute change in dominant-hand HGS between hospital admission and discharge, calculated as the difference between the maximum dominant-hand value recorded at discharge and the corresponding baseline measurement. Daily HGS measurements obtained throughout hospitalization will be analyzed as secondary exploratory outcomes to characterize temporal patterns of muscle deterioration.

#### 3.3.2. Secondary Outcome Measure

The non-dominant hand and bilateral analyses, as well as sEMG parameters, bioimpedance, biomarkers, and questionnaires, will be considered secondary/exploratory outcomes, consistent with the use of exploratory endpoints for hypothesis generation without confirmatory intent [17,22].

#### 3.3.3. Pre-Specified Covariates (For Adjustment)

To minimize overfitting in multivariable models, a limited set of clinically relevant predictors will be pre-specified before the start of the analysis. These were selected based on their widespread use as prognostic or confounding factors in oncology: age, sex, functional status measured by ECOG, cancer histological type, presence of major comorbidity, and length of hospital stay [23,24,25]. Age and ECOG functional status have been consistently associated with survival and treatment tolerance in multiple oncology cohorts, with significantly unfavorable hazard ratios for older patients and ECOG 2–4 compared to ECOG 0–1 [24,25,26]. Sex and cancer histological type are routinely used as adjustment variables to capture biological differences and treatment response across subgroups [23,24,25]. Finally, the burden of major comorbidity has been linked to both higher dropout rates in clinical trials and poorer overall survival, justifying its inclusion as an adjustment covariate in prognostic and functional response models [27,28]. Length of hospital stay was additionally included because prolonged hospitalization may increase exposure to physical inactivity, systemic inflammation, nutritional deterioration, and other factors associated with accelerated muscle loss.

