Prior to analysis, all recordings will undergo visual inspection and quality-control procedures. Signal segments will be excluded if they exhibit evidence of electrode displacement, signal saturation, excessive baseline noise, movement artifacts, abrupt signal discontinuities, or other technical abnormalities that may compromise signal interpretation. When multiple epochs are available, only artifact-free segments meeting predefined quality criteria will be included in the final analysis.

To ensure reliability in the bedside hospital setting, all evaluators will undergo standardized training, and all procedures will follow predefined operating protocols. Electrode placement sites will be systematically documented to ensure consistent positioning across repeated measurements.

Safety Monitoring and Adverse Event Recording

All assessments will be performed only when participants are considered clinically stable by the attending medical team. Prior to each testing session, patients will be screened for contraindications, including acute clinical deterioration, uncontrolled pain, severe fatigue, hemodynamic instability, active infection requiring urgent intervention, or any condition that may compromise safe participation.

Adverse events occurring during or immediately after testing will be documented, including dizziness, excessive fatigue, pain exacerbation, musculoskeletal discomfort, cardiovascular symptoms, falls, or any unexpected clinical event. The severity, duration, and relationship to the assessment procedure will be recorded.

Testing will be immediately discontinued if participants report intolerable discomfort, request termination, exhibit signs of excessive fatigue, develop cardiovascular symptoms, or if the research team determines that continuation may compromise safety. Participant safety will always take precedence over protocol completion.

Serum biomarkers—Basic Panel

Laboratory assessments will be performed at hospital admission and discharge. In cases where daily blood tests are required for clinical reasons, these additional results will be incorporated into the longitudinal analysis.

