### 3.9. Statistical Analysis

The primary endpoint is the absolute change in dominant-hand handgrip strength (HGS) between hospital admission and discharge. The primary analysis will consist of a within-subject comparison of admission and discharge HGS values. Mean change scores and corresponding 95% confidence intervals will be reported. Statistical significance will be assessed using a paired *t*-test for normally distributed data or the Wilcoxon signed-rank test when normality assumptions are not met. All tests will be two-sided, with a significance level of *p* < 0.05. Exploratory longitudinal analyses will be performed using linear mixed-effects models to characterize daily trajectories of handgrip strength (HGS) and sEMG parameters during hospitalization while accounting for repeated measurements within participants and unequal numbers of observations across individuals. These analyses are intended to describe temporal patterns of muscle function and neuromuscular fatigue and are considered secondary and exploratory. They do not constitute the primary analysis of the study. Missing data due to discharge, clinical deterioration, medical procedures, symptom burden, or death will be handled under the missing-at-random (MAR) assumption inherent to mixed-effects modeling. The frequency and reasons for missing observations will be systematically documented across all outcome domains.

The primary endpoint is the absolute change in dominant-hand handgrip strength (HGS) between hospital admission and discharge. The primary analysis will consist of a within-subject comparison of admission and discharge HGS values. Mean change scores and corresponding 95% confidence intervals will be reported. Statistical significance will be assessed using a paired *t*-test for normally distributed data or the Wilcoxon signed-rank test when normality assumptions are not met. All tests will be two-sided, with a significance level of *p* < 0.05.

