Associations between functional outcomes, sEMG parameters, and biomarkers will be explored using multivariable regression models adjusted for pre-specified covariates (age, sex, ECOG performance status, cancer type, comorbidity burden, and length of hospital stay). Given the exploratory nature of the study and the planned sample size, these analyses will be interpreted cautiously and will primarily serve to estimate effect sizes and identify candidate variables for future confirmatory studies. The contraction intensity used during each sEMG fatigue assessment (65% or 50% MVC) will be recorded and considered during data interpretation. Because contraction intensity may influence neuromuscular fatigue parameters, exploratory analyses will account for intensity level and, when sample size permits, stratified analyses will be performed. No direct comparison between intensity conditions is planned, and results obtained under different intensity levels will be interpreted cautiously.

Participants with both admission and discharge handgrip strength (HGS) measurements will be included in the primary endpoint analysis. The frequency and reasons for missing discharge assessments, including early discharge, transfer to another facility, clinical deterioration, or death, will be systematically documented.

Sensitivity analyses will compare baseline demographic and clinical characteristics between participants with complete and incomplete primary endpoint data. When appropriate, exploratory analyses based on the last available HGS measurement obtained during hospitalization will be conducted to assess the robustness of the primary findings. Results from these analyses will be interpreted cautiously due to the potential for informative missingness.

Hydration-related variables, including edema, ascites, and recent intravenous fluid administration, will be considered in the interpretation of bioelectrical impedance analysis (BIA)-derived outcomes and may be incorporated into sensitivity analyses when clinically relevant. Additional clinical variables may also be included in exploratory or sensitivity analyses when justified and supported by sufficient data availability.

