Sensitivity analyses will be performed when substantial missing data or potential sources of bias are identified, to assess the robustness of the findings. Attention will be given to variables in which missingness may be related to clinical status or disease severity. Biomarker measurements obtained only when clinically indicated will be analyzed descriptively and interpreted with caution due to potential non-random availability across participants.

Overall, all association analyses are exploratory in nature and intended to generate hypotheses and provide preliminary estimates of potential relationships for future confirmatory studies. The number of repeated assessments may vary among participants depending on hospitalization duration and clinical feasibility.

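### Length of stay, known only at discharge, is in the fixed adjustment set of the exploratory association models, so coefficients for admission predictors may not be total associations with HGS change

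*Protocol article*

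**What the plan says.** Section 3.3.3 fixes six adjustment variables: age, sex, ECOG, histological type, major comorbidity and length of stay. It introduces them together: "These were selected based on their widespread use as prognostic or confounding factors in oncology". Stay has its own justification: "Length of hospital stay was additionally included because prolonged hospitalization may increase exposure to physical inactivity, systemic inflammation, nutritional deterioration", with other contributors to faster muscle loss.

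Section 3.9 applies the set to the regressions linking functional outcomes, sEMG parameters and biomarkers. These models are "adjusted for pre-specified covariates (age, sex, ECOG performance status, cancer type, comorbidity burden, and length of hospital stay". No version without stay is named, and predictors measured at admission are not separated from changes over the stay.

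The exploratory objective in Section 2.2 is to "identify candidate clinical, functional, electrophysiological, and biochemical variables associated with greater muscle deterioration during hospitalization". Under Section 3.5, questionnaires, HGS, bioimpedance, sEMG and blood sampling all take place on Day 1, and the full assessment is repeated at discharge. Patients are "evaluated from admission to discharge" (Section 3.1).

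The primary analysis carries no covariates: "The primary analysis will consist of a within-subject comparison of admission and discharge HGS values". Section 3.9 also states that "all association analyses are exploratory in nature and intended to generate hypotheses".

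**The concern.** Five of the six covariates can be known at admission. The sixth cannot: stay is the length of follow-up and is fixed only when the discharge HGS is taken. The plan's reason for including it describes a route to the outcome, in which a longer stay brings more exposure to causes of muscle loss. That does not make stay a confounder of something measured on Day 1, because stay comes afterwards.

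Suppose an admission marker, for example a high CRP, goes with a longer stay. Part of its association with HGS loss may then run through the stay, and adjusting for stay takes that part out. If weakening itself prolongs the stay, adjustment can also bias what remains.

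Section 3.9 wants these models to estimate effect sizes and pick candidate variables for later confirmatory studies. A coefficient that leaves out the part acting through stay, without saying so, could make a candidate look weaker than it is.

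**Working it through.** The plan gives no figure on this point. Its only calculation, the sample size, concerns the primary outcome and does not involve stay.

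**Inputs from the protocol article**
- Stay equals follow-up time and ends when the outcome is measured (Section 3.1).
- Stay is linked to muscle loss by the plan's own rationale (Section 3.3.3).
- Predictors are available both as admission values and as changes. For biomarkers: "Laboratory assessments will be performed at hospital admission and discharge" (Section 3.4).
- The target is 50 participants (Section 3.2).

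**Assumed inputs.** The documents do not give the effect of a predictor X on stay L (path a), the effect of L on HGS change Y (path b), or the direct effect of X on Y (c). Every size below rests on assumed values for these.

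**1. X is measured at admission and affects stay (X → L → Y).** In a linear model the total association is c + ab, the coefficient adjusted for L is c, and the share removed is ab/(c + ab).

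In kilograms, the shift is (days of stay per SD of X) × (kg lost per day):
- Low: 0.5 × 0.1 = 0.05 kg per SD.
- High: 1.5 × 0.3 = 0.45 kg per SD. With a direct effect of −0.50, the total is −0.95 and the adjusted coefficient −0.50. In 2,000 simulated studies of 50 patients the averages were −0.97 and −0.52, a fall of about 46%.

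With X and L scaled to SD 1, Y to unit residual SD, and c = −0.3:

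| a | b | Total c + ab | Adjusted | Removed |
|---|---|---|---|---|
| 0.2 | −0.2 | −0.34 | −0.30 | 0.04/0.34 = 12% |
| 0.3 | −0.3 | −0.39 | −0.30 | 0.09/0.39 = 23% |
| 0.5 | −0.5 | −0.55 | −0.30 | 0.25/0.55 = 45% |

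If a = 0, then ab = 0 and nothing is removed.

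**2. X is a change over the same stay, and stay drives both X and Y.** With the same path values, the unadjusted slope is −0.34 to −0.55 against a true −0.30. Adjusting for stay restores −0.30, so here adjustment is the better choice.

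**3. Both X and the decline in HGS prolong the stay.** With L = aX + bY + error (unit error variance), the adjusted coefficient is c − b(a + bc)/(1 + b²):
- a = 0.3, b = −0.3: −0.30 + 0.3 × 0.39/1.09 = −0.19.
- a = 0.5, b = −0.5: −0.30 + 0.5 × 0.65/1.25 = −0.04.

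The true value is −0.30 in both. Simulation with 400,000 observations agreed with all three cases.

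One covariate list therefore gives three results. Adjustment removes part of the association in case 1, corrects a bias in case 2 and creates one in case 3. Section 3.9 does not tell these uses apart.

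**The case against.** The strongest reply is that only half of the mediating path is in the document. Section 3.3.3 links a longer stay to muscle loss; nowhere does the plan say that an admission marker lengthens the stay. Its sentence places stay upstream of inflammation and nutritional decline, which favours adjustment when changes in those markers are studied. This stands, and it makes the concern conditional.

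Stay is also the interval over which HGS change accrues. Without it, a coefficient mixes faster loss with longer observation; with it, patients are compared at equal stay. Both are legitimate quantities. This stands too, and it is a reason to show both models and label them.

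The precision is low. With an assumed residual SD of 3.5 kg and 50 patients, the standard error of a coefficient is roughly 3.5/√50 = 0.49 kg, so even the 0.45 kg shift is under one standard error. But the shift is systematic, and the plan's general caution about sample size and overfitting does not tell a reader that part of the association has been taken out.

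It may also be said that the choice of marker values and extra models belongs in a statistical analysis plan. That is fair for details, but the article has already fixed the covariate set, and an analysis plan that followed it would inherit the issue.

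Three stronger inferences are not supported:
- A reader might infer that the plan treats stay as a baseline variable. It calls the covariates prognostic or confounding and states openly that stay reflects exposure.
- A reader might infer that the study fails its purpose of early identification. The primary objective is to quantify HGS change. Section 3.2 says the sample was not intended to power predictive modelling, and Section 6 calls it insufficient for predictive or risk-stratification models.
- A reader might infer that adjustment for stay is wrong throughout. Case 2 shows otherwise.

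**Conclusion.** The point holds for one class of model: exploratory regressions of HGS change on predictors measured at admission. If such a predictor also affects stay, the planned coefficient is not its total association and can be smaller or distorted. The shift is 0.05 to 0.45 kg per SD, or about 12% to 45% on the standardized scale, all under assumed path strengths. The 46% fall belongs to the high end of the assumed range and is not an expected value. Loss of association is possible but is not established by the documents. The primary paired analysis and the sample size do not change. This is a cheap improvement to exploratory analyses and does not threaten the main result.

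**What to change.** In Section 3.9, separate two kinds of association model.

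- **Admission predictors.** Report a model adjusted only for age, sex, ECOG, cancer type and comorbidity. Beside it, report a labelled model that adds length of stay. State that the first estimates the total association and the second the association at equal length of stay.
- **Change against change over the same stay.** Keep length of stay, described as a time-at-risk term.

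The cost is a few sentences and one extra model column, with no new data. The downside is that the model without stay mixes faster loss with longer observation, which is why the two should be read side by side.
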